## Abstract

**Background:**

NHS Health Checks is a new program for primary prevention of heart disease, stroke, diabetes, chronic kidney disease, and vascular dementia in adults aged 40 to 74 years in England. Individuals without existing cardiovascular disease or diabetes are invited for a Health Check every 5 years. Uptake among those invited is lower than anticipated.

**Method:**

The project is a three-arm randomized controlled trial to test the hypothesis that enhanced invitation methods, using the Question-Behaviour Effect (QBE), will increase uptake of NHS Health Checks compared with a standard invitation. Participants comprise individuals eligible for an NHS Health Check registered in two London boroughs. Participants are randomized into one of three arms. Group A receives the standard NHS Health Check invitation letter, information sheet, and reminder letter at 12 weeks for nonattenders. Group B receives a QBE questionnaire 1 week before receiving the standard invitation, information sheet, and reminder letter where appropriate. Group C is the same as Group B, but participants are offered a £5 retail voucher if they return the questionnaire. Participants are randomized in equal proportions, stratified by general practice. The primary outcome is uptake of NHS Health Checks 6 months after invitation from electronic health records. We will estimate the incremental health service cost per additional completed Health Check for trial groups B and C versus trial arm A, as well as evaluating the impact of the QBE questionnaire, and questionnaire plus voucher, on the socioeconomic inequality in uptake of Health Checks.

The trial includes a nested comparison of two methods for implementing allocation, one implemented manually at general practices and the other implemented automatically through the information systems used to generate invitations for the Health Check.

**Discussion:**

The research will provide evidence on whether asking individuals to complete a preliminary questionnaire, by using the QBE, is effective in increasing uptake of Health Checks and whether an incentive alters questionnaire return rates as well as uptake of Health Checks. The trial interventions can be readily translated into routine service delivery if they are shown to be cost-effective.

**Trial registration:**

Current Controlled Trials ISRCTN42856343. Date registered: 21.03.2013.

## Background

### The burden of cardiovascular disease

Cardiovascular disease (CVD), including coronary heart disease and stroke, is the leading cause of death in the UK [1]. In 2010, more than 45,000 individuals who were younger than 75 years died of CVD [1]. The prevalence of Type 2 diabetes, a risk factor for CVD, has increased [1], with more than 2.5 million living with a diagnosis of diabetes in England [2]. In 2008 through 2009, almost 2 million adults in England were registered as having chronic kidney disease [3]. CVD was estimated to cost the UK healthcare system £9 billion in 2009 [4]. The risk of CVD can be reduced through lifestyle and pharmacologic interventions tailored to individuals’ risk-factor profiles. A socioeconomic gradient in mortality exists from CVD, CHD, and stroke, with individuals from more-deprived backgrounds being at increased risk of death [1].

### The NHS Health Check

NHS Health Checks, a new cardiovascular disease primary prevention program, has been fully implemented in England since April 2011 [5]. All adults aged 40 to 74 years, without existing cardiovascular disease or diabetes, are invited for a five-yearly assessment of their risk-factor profile. The aim of the program is to identify people who are at increased risk of heart disease, stroke, diabetes, CKD, or vascular dementia so that graded intervention may be offered based on the individual’s cardiovascular risk score. The NHS Health Check program is estimated by the UK Department for Health to have the potential to prevent 2,000 deaths and 9,500 nonfatal myocardial infarctions and strokes each year [6]. The risk assessment is provided free at the point of delivery to any eligible individual, so it has the potential to reduce inequalities in CVD as long as uptake is equitable.

### Economic modeling for cost-effectiveness estimates

The Department of Health’s decision to introduce NHS Health Checks was based on health economic modeling suggesting that the program would be cost-effective [6]. It was estimated that the program would cost less than £3,000 per quality-adjusted life year; (QALY) [6]. The economic model assumed overall program uptake of 75%, informed by uptake data from the national breast-screening program. However, uptake appears to be <75%, with program data for 2013/2014 showing that 49% of people who were offered an NHS Health Check received one [7]. The few studies that have examined whether socioeconomic differences exist in uptake of NHS Health Checks have reported conflicting findings [8, 9]; however, evidence suggests a socioeconomic gradient in cervical and breast cancer screening attendance in the UK [10–12].

### Interventions to increase uptake of health checks

Jepson *et al.*
[13] published a systematic review of 190 trials of interventions used to increase uptake of screening for a variety of conditions [13]. Interventions that targeted individuals and that comprised enhanced methods of inviting patients seemed to be effective at increasing screening uptake, including invitation letters, appointments, telephone calls and patient reminders. None of the interventions in this review aimed to increase uptake of a general CVD risk assessment. In a study of blood pressure screening, McDowell *et al.*
[14] reported that patients who received an invitation letter were more likely to attend than were controls, and those who received a telephone invitation were more likely to attend than were those who received a letter. In a study of cholesterol testing [15], telephone invitations did not increase uptake compared with controls, nor did financial incentives, compared with controls.

Two recent studies evaluated interventions to increase uptake of CVD prevention. One Canadian trial [16] found that patients were more likely to attend if they were invited by telephone than by letter. Telephone invitations to promote uptake are difficult to implement on a large scale, as would be required for a national screening program. Another study of patients from one general practice examined the effect of sending a preliminary questionnaire before patients being invited for a health check [17]. This enhanced invitation method increased uptake, with 68.3% of the intervention group having a health check compared with 53.5% of the control group who received no intervention. The authors invoked the Question-Behaviour Effect (QBE), which suggests that asking questions about a behavior increases the likelihood that the behavior will be performed. Previous studies have shown that the QBE increases engagement in health-related behaviors, including cervical screening uptake in the UK [18, 19]. The effect is greater if individuals are asked if they would regret not attending for screening and if individuals complete and return the questionnaire [17, 19].

### Financial incentives to increase response rates to questionnaires

Strong evidence suggests that financial incentives for questionnaire return increase response rates. A systematic review, including 94 trials with a pooled total of 160,004 participants, found that the odds of returning a postal questionnaire were almost doubled if a financial incentive was offered [20]. As the Question-Behaviour Effect is greater among individuals who return a questionnaire [17], incentivizing questionnaire return may increase the size of any effect of a questionnaire on uptake of the NHS Health Check. A meta-analysis of 85,671 participants in 88 randomized trials of financial incentives to increase response rates for mailed questionnaires reported a significant increase in response rates for incentives up to the value of $5 [21].

### What is the potential impact on socioeconomic inequalities in uptake?

Death rates from coronary heart disease are highest in areas of greatest deprivation [1], so considering socioeconomic inequalities in the evaluation of any intervention to increase uptake of NHS Health Checks is important. Although evidence suggests that enhanced invitation methods, such as a QBE-based questionnaire, increase uptake of screening and performance of health-related behaviors, we do not know their impact on the NHS Health Checks, a relatively new program. The impact of the QBE on inequalities in uptake is also unknown. Individuals experiencing greater levels of deprivation may find it more difficult to convert their positive attitudes toward Health Checks, and their intentions to attend, into action. One of the possible mechanisms of action of the QBE is that it makes individuals’ attitudes more cognitively accessible and thus may increase the likelihood that individuals from deprived backgrounds attend. Alternatively, although we do not know if level of deprivation influences attitudes toward NHS Health Checks, evidence from cancer screening suggests that individuals experiencing greater levels of deprivation perceive fewer benefits and greater barriers to attending [22].

The QBE is stronger for individuals with positive attitudes toward, and intentions for, the behavior [17]; therefore the QBE may enhance inequalities in uptake, if any do exist. The offer of a financial incentive may increase questionnaire return rates only among those with already positive attitudes toward NHS Health Checks, so should result in increased uptake. However, if the offer of a financial incentive increases questionnaire return rates among those with less-positive attitudes, it is likely to have a lesser impact on uptake.

Little research examines how and if incentives influence uptake of screening differentially across deprivation [23]. The offer of a financial incentive may be most attractive for individuals who are experiencing deprivation and so may increase the strength of the QBE on Health Check uptake, particularly in individuals from deprived backgrounds. It will be important to consider inequalities in uptake in any investigation of the impact of the QBE on uptake of NHS Health Checks.

### Objectives

The aim of this research is to determine whether enhanced invitation methods, in using the QBE, lead to increased uptake of NHS Health Checks. The specific objectives of this research are as follows:To implement a randomized controlled trial (RCT) with individual participants who are eligible for NHS Health Checks as the unit of allocation. The trial will compare the effects of: standard invitation only; QBE questionnaire followed by standard invitation 1 week later; QBE questionnaire, with offer of retail voucher as incentive for questionnaire completion, followed by standard invitation 1 week later. The intervention effect will be evaluated by using the primary outcome of whether each individual completed the NHS Health Check within 182 days (6 months) of the standard invitation being sent.To estimate the incremental health service cost per additional health check completed for the QBE questionnaire, and the QBE questionnaire-plus-voucher trial arms, in comparison with the standard invitation.To evaluate the impact of the QBE questionnaire, and the QBE questionnaire plus voucher, on inequality in uptake of Health Checks between most- and least-deprived areas of residence based on the Indices of Multiple Deprivation (IMD 2010) score by postcode of residence.

## Methods

### Trial design

Three-arm superiority randomized controlled trial with equal allocation to each arm (see Figure 1 for the trial flow diagram).

**Figure 1 Fig1:**
[figure not shown]
**Trial flow diagram.**

### Setting and participants

The trial is being implemented in two London Boroughs, which are ranked 14th and 16th most-deprived local authorities in England [24]. Both boroughs are typical of areas that are in need of intervention to increase the number of individuals attending for their NHS Health Check, as uptake is below the national average (49%) [7]. In 2013/2014, 32% of individuals invited for a Health Check attended in one borough, and 38%, in the other [7].

All general practices in these boroughs are eligible and asked to consent to their patients participating in the trial. Patients are included in the trial only if their practice has provided consent. Consent to use questionnaire data is presumed, based on participants returning a questionnaire. All participants in the consented practices who are eligible to receive an NHS Health Check are included in the trial, with no exceptions from randomization or analysis.

Individuals are eligible for an NHS Health Check if they are aged between 40 and 74 years and have no existing CVD-related comorbidities and are not already prescribed antihypertensive drugs or statins. Individuals are invited for a Health Check through a cross-borough call and recall system, organized at a central unit that serves both boroughs. Each month, eligible patients are identified centrally and a pre-notification list of patients is sent to each practice for them to perform a second check for eligibility/suitability. After this, the list is considered to be ”clean”, and these patients are invited for an NHS Health Check in that month by standard invitation letter. The individual clean lists for each participating practice is the sampling frame for this trial.

### Recruitment and randomization

We are implementing two recruitment methods. For 12 purposively selected practices (from those who consent), researchers visit each practice monthly and allocate participants to each trial arm by using a pregenerated randomization list (in-practice method). Each month, the trial statistician draws up the randomization lists stratified by general practice. As all patients within a practice are assigned at one time, and to minimize the imbalance in participants between arms, random allocation uses blocks of three. The preordered randomization list is matched by the researchers to the existing order of the clean eligible patient list. For six different purposively selected practices, randomization is performed automatically by using a simple randomization procedure programmed into the information system that is used to manage the Health Check Program (automated method). For the automated method, simple randomization, stratified by practice, is being used. A randomization program has been written, and participants are automatically assigned a study ID and group allocation when the clean lists are electronically approved. Each practice is participating in the trial for a minimum of 12 months to allow seasonal variation in uptake of Health Checks.

### Interventions

Group A receives the standard invitation letter for a NHS Health Check, sent from the central unit that organizes Health Check invitations. This comprises a single-page letter from the individuals’ GPs, inviting them to make an appointment at their general practice to receive the Check or to visit a local participating pharmacy, plus an information sheet. Individuals are sent a reminder letter if they do not attend for a Health Check within 12 weeks of their first invitation.

Group B: Participants are sent the QBE questionnaire, with prepaid return envelope and covering letter 7 days before they are sent the standard NHS Health Check invitation letter and information sheet (plus reminder letter at 12 weeks, where appropriate). The QBE questionnaire is a two-page, eight-item questionnaire with one example question at the beginning. Six questions are derived from Theory of Planned Behavior [25] concepts, and two questions are based on the notion of anticipated regret. All questions are on a 7-point scale and have high readability. The questionnaire was subjected to feasibility and acceptability testing, with five individuals involved in the delivery of the NHS Health Checks program and 15 individuals from the local population in the target age range for a Health Check. Based on this feedback, the questionnaire was further refined before being used in the trial.

Group C: Participants are sent the QBE questionnaire, with prepaid return envelope and covering letter 7 days before they are sent the standard NHS Health Check invitation letter and information sheet (plus reminder letter at 12 weeks, where appropriate). The covering letter differs from that received by Group B, as participants are offered a £5 retail voucher as an incentive to return the questionnaire.

### Outcomes

The primary outcome is uptake of NHS Health Checks 182 days (6 months) after the standard invitation. Secondary outcomes include uptake of NHS Health Checks 91 days (3 months) after standard invitation and time elapsed between participants receiving the standard invitation and Health Check (among those who attend). Outcomes are extracted from general practice records by members of the research team by using nationally specified READ codes to record completion of NHS Health Checks. Participants’ postcodes are converted into an Indices of Multiple Deprivation score (IMD 2010) as a marker of deprivation.

The study received ethical approval from the NRES Committee London, London Bridge committee (13/LO/01/97).

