### Statistical methods

The analysis will be on an intention-to-treat basis and will include all patients who are randomized, regardless of subsequent actions (for example, if the questionnaire was not sent out, participants will still be analyzed in the group to which they were randomized). For participants who die or leave their general practice within 6 months of the standard invitation, we will use the Health Check uptake status at the end of registration as their outcome.

In an individually randomized trial, Health Check uptake may vary between general practices, as, for example, if a practice nurse follows-up patients for an appointment. We will quantify the extent of between-practice variation by tabulating the outcome by general practice and estimating an intraclass correlation coefficient by using analysis of variance.

To adjust for practice-effect in the primary analysis, we will fit a marginal model by using the method of generalized estimating equations (GEEs), allowing for clustering by practice by using an exchangeable correlation structure and model-based variance estimates, as the number of practices is relatively small [27]. Covariates will be age, gender, month of invitation, deprivation quintile, and arm comparing outcomes between arms A versus B, A versus C, and B versus C, with adjustment for multiple comparisons.

The GEE model will be implemented by using the binomial family and an identity link to estimate the adjusted risk difference. Because we are primarily interested in absolute differences in NHS Health Check uptake, rather than in relative measures such as odds ratios, we will implement covariate adjustment by the method of inverse probability weighting by using the propensity score as suggested by Ukoumunne *et al*. [28]. Interaction terms will be tested, and, where appropriate, intervention effects will be estimated by subgroup. The slope index of inequality (SII) [29] will be used as a metric to estimate the difference in screening uptake between the least- and the most-deprived quintiles (local IMD scores will be classified into quintiles of the distribution of IMD scores in England for reference), and we will test whether SII differs between trial arms.

All estimates will be presented with 95% confidence intervals and *P* values. The trial will be reported according to CONSORT recommendations.

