### Secondary analyses

To understand the processes of responding to the intervention, analyses will be implemented to determine whether completing the QBE questionnaire, as opposed to receiving but not completing the questionnaire, is necessary to obtain the observed effects. We will compare the proportions of patients who attend Health Checks among participants who received and completed the questionnaire for the QBE arm (completers) and the QBE + incentive arm (incentive-completers), as well as participants in the QBE arm who received but did not complete the questionnaire (noncompleters) and participants in the QBE + incentive arm who received but did not complete the questionnaire (incentive-noncompleters), and those who did not receive the questionnaire.

We will also examine whether having higher or more-positive cognitions (that is, attitude, subjective norms, perceived behavioral control, anticipated regret, intentions) about the Health Check, when completing the QBE questionnaire is associated with increased rates of attendance. Therefore, we will compare the proportions of patients who attend Health Checks for positive completers (those with high scores on the cognitions) and negative completers (those with low scores on the cognitions). If significant differences in uptake appear between the QBE and QBE + incentive arms, we will examine whether these are mediated by differences in cognitions [30].

The response rate to the QBE questionnaire will be analyzed both overall, for each treatment group, and by deprivation quintile. The distributions of responses to questionnaire items will be evaluated by deprivation quintile. We plan to access the results of the participants’ Health Checks, in terms of level of cardiovascular risk, and compare these by trial arm. We will compare Health Check results for questionnaire responders and nonresponders. These analyses will thus describe the pattern of response to the intervention in terms of both deprivation category and level of cardiovascular risk.

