Secondary analyses to examine whether outcomes and intervention effects vary by deprivation quintile, gender, or age-group will be performed in a similar manner as stated earlier and will include exploring interaction effects. The delay in uptake between arms will be examined by using time-to-event analysis. The duration between the date the invitation was sent and the booked appointment will be calculated. Differences will initially be visually assessed by using Kaplan-Meier curves, and then an appropriate time-to-event model with robust variance estimates allowing clustering by practice will be fitted, adjusting for age, gender, month, and deprivation quintile.

To evaluate the consistency of estimates obtained by using the two different randomization methods, subgroup analyses will be performed for each randomization method separately. A meta-analysis will be performed, by using each participating general practice as the unit of analysis, with results pooled for each randomization method separately and across all practices. A test for heterogeneity will be performed.

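### Time to Health Check is defined only among attenders, a group the intervention is meant to change, and the analysis text names a different end point (booked appointment) and no other population

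*Protocol article*

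**What the plan says.** The Outcomes section of the protocol article gives the secondary outcome as "time elapsed between participants receiving the standard invitation and Health Check (among those who attend"). Outcomes are taken from practice records "by using nationally specified READ codes to record completion of NHS Health Checks".

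The Secondary analyses section sets out the analysis: "The delay in uptake between arms will be examined by using time-to-event analysis", and then "The duration between the date the invitation was sent and the booked appointment will be calculated". The method is Kaplan-Meier curves, after which "an appropriate time-to-event model with robust variance estimates allowing clustering by practice will be fitted", adjusted for age, gender, month and deprivation quintile. Neither the population nor the censoring rule is stated there.

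The Statistical methods section has a general rule: "The analysis will be on an intention-to-treat basis and will include all patients who are randomized, regardless of subsequent actions". For the primary GEE it chooses model-based variance because there are few practices.

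The Secondary analyses section also plans to obtain Health Check results "in terms of level of cardiovascular risk, and compare these by trial arm".

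**The concern.** Whether a person attends is the primary outcome, and the trial's hypothesis is that the questionnaire raises it. Selecting attenders therefore selects on a post-randomisation event that differs by arm if the intervention works. The active-arm attenders would then include people with no counterpart among the control attenders. If those people attend earlier or later than the rest, the comparison shows a speed-up or a delay although nobody who would have attended anyway changed timing. Adjusting for age, gender, month and deprivation removes only the part of this selection that those variables capture.

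A separate fault is that the two sections describe different intervals. One ends at the Health Check, the other at a booked appointment, and a booking is not a completed check. The Interventions section also lets invitees go to a participating pharmacy, so some completed checks may have no practice booking.

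At stake is one secondary result: whether the questionnaire, with or without the voucher, speeds or delays attendance.

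**Working it through.** **The plan's own figure.** None is given for the time outcome. The sample size supplies the design effect, so it was checked first. Inputs from the Sample size section are 50% uptake, a 4-point difference, 90% power and 5% Bonferroni-corrected for three comparisons (0.05/3 = 0.0167; two-sided assumed).

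- n = [z(1-α/2)·√(2p̄q̄) + z(1-β)·√(p1q1 + p2q2)]² / δ² = [2.394·√0.4992 + 1.282·√0.4984]² / 0.04² ≈ 4,213.
- With continuity correction: (n/4)·[1 + √(1 + 4/(nδ))]² ≈ 4,263 per arm. This matches the plan, and 3 × 4,263 = 12,789.

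**Who is compared.** An analysis of all randomised participants compares 4,263 with 4,263. An attender-only analysis at 50% v 54% compares about 4,263 × 0.50 ≈ 2,132 with 4,263 × 0.54 ≈ 2,302. If nobody is deterred, the share of active-arm attenders who attend only because of the intervention is s = (pB - pA)/pB:

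| Uptake A v B | Source of A | s |
|---|---|---|
| 50% v 54% | design assumption | 7.4% |
| 38% v 42% | one borough, 2013/2014 | 9.5% |
| 32% v 36% | other borough, 2013/2014 | 11.1% |

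**Shift in mean time among attenders.** Assume those who would attend anyway average 50 days in every arm, so the timing effect on them is zero, and let the extra attenders average m days. The attender-only difference is s·(m - 50). The timings are assumptions; the documents give none. The last two columns are rejection rates at nominal 5% from a simulation of 1,500 runs per row, with 4,263 per arm and a simple comparison of means.

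| m (days) | Difference, 50% v 54% | Difference, 35% v 39% | Rejection, 50% v 54% | Rejection, 35% v 39% |
|---|---|---|---|---|
| 20 | -2.2 | -3.1 | 44% | 56% |
| 50 | 0 | 0 | 5% | 5-6% |
| 80 | +2.2 | +3.1 | 43% | 54% |
| 110 | +4.4 | +6.2 | 95% | 99% |

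**The opposite error.** Assume a constant hazard λ that gives 35% uptake by day 182: λ = -ln(0.65)/182. A true hazard ratio of 1.15 raises uptake to 1 - 0.65^1.15 = 39.1%. The mean time among attenders is 1/λ - 182(1 - p)/p, where p is uptake by day 182. This gives 84.5 days v 83.5 days, so a real effect on the rate of attendance almost disappears.

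**Start and end points, side by side.** Outcomes: invitation received, to Health Check. Secondary analyses: invitation sent, to booked appointment. Received versus sent is loose wording, since Objectives already starts the primary outcome's clock when the invitation is sent. Check versus booking is a real difference, and only completion codes are named as a source.

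**Variance.** There are 12 + 6 = 18 practices (Recruitment and randomization). In a simplified linear analogue with 18 equal clusters (40,000 runs), an uncorrected sandwich variance with a normal reference rejects about 7.5% of the time at nominal 5%. With a G/(G - 1) correction and t on 17 degrees of freedom it rejects about 5.0%. No time-to-event model was simulated.

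**The case against.** The strongest reply is that the three sections can be read together. An elapsed time is observed only in people who attend, so the parenthesis in Outcomes may just describe the data. Kaplan-Meier curves and a time-to-event model would then be applied to everyone randomised, as the intention-to-treat rule requires, with non-attenders censored. That analysis would keep the randomised comparison, and censoring details may sit in an analysis plan that is not shown. This reply stands in part: a reader might infer that the planned delay analysis is certainly non-randomised, and the text does not establish that. It does not remove the point, because the only population the article states for this outcome is attenders.

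Three further inferences go too far.

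- The end-point mismatch does not itself break randomisation. It is an inconsistency of definition.
- A reader might conclude that the robust variance will inflate the type I error to 7-8%. That follows only for an uncorrected sandwich with a normal reference, which the protocol does not specify. What remains is that two sections treat the same 18 practices differently.
- The comparison of cardiovascular risk by arm also uses attenders, but its stated purpose is to describe the pattern of response. Who attends in each arm is the question there, so it is not a flawed effect estimate.

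Finally, the shifts above depend on assumed timings. If the extra attenders have the same timing as the others, there is no bias.

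**Conclusion.** The point holds as a definitional fault in a secondary outcome. Analysed as Outcomes defines it, the delay comparison would not be protected by randomisation. About 7% of active-arm attenders at the design effect, and 10-11% at local uptake plus 4 points, would have no control counterpart, assuming nobody is deterred. In the examples the resulting shift runs from about -3 to +6 days. Neither size nor sign can be predicted, and the shift may be zero. Secondary analyses permits a valid reading but does not state it, and it uses a booking end point with no named source. The variance inconsistency is real but minor. The primary uptake analysis and its sample size are unaffected.

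**What to change.** State one outcome in both Outcomes and Secondary analyses: days from the date the standard invitation was sent to the date of the completed Health Check. Specify:

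- **Population:** all randomised participants, in line with Statistical methods.
- **Censoring:** non-attenders at 182 days, or at death or deregistration if earlier.
- **Display and model:** Kaplan-Meier cumulative uptake by arm, then the time-to-event model with the covariates already listed (age, gender, month, deprivation quintile).
- **Practice:** handle it consistently with the primary analysis, for example by stratifying the model by practice with model-based variance, or use a robust variance with a small-sample correction.
- **Descriptive only:** time summaries among attenders, and the cardiovascular-risk comparison by arm.

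Remove the booked-appointment end point, or name its data source and label it as a separate measure. The cost is a wording change. The 91-day and 182-day uptake outcomes already require the timing of the completed check, so no new data collection should be needed.
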